### Participants

Prior to hospital discharge, physicians will inform the patients of the purpose and methods of the study. The inclusion criteria will be the following: age ≥18 years; recovery from first ischemic or hemorrhagic stroke in all brain areas; stroke within <6 months; Functional Ambulation Classification score ≥2; patient monitoring by the post stroke interventional mobile team (HEMIPASS); and registration with the French social security system.

The exclusion criteria for both groups will be the following: stroke recurrence; disorders limiting gait skills before or after stroke; cognitive disorders impeding comprehension of physical activity education i.e. aphasia indicated by a Boston Diagnostic Aphasia Examination (BDAE) score <2; non-controlled hypertension; inability to complete questionnaires; cardiopulmonary pathology preventing effort completion; non-signature of written consent; involvement in other research; legal guardianship; and pregnancy.

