### Outcomes

Outcome assessments will be performed after hospital discharge (T0), at 6 months (T1), and at 12 months (T2). The PA therapist will confirm the T1 and T2 medical appointments 3 weeks before the due date to avoid time bias. If the participant cannot attend the medical appointment, it will be delayed for a maximum of 3 days. The same practitioners, a medical doctor and a professional PA therapist will perform all assessments at the University Hospital of Limoges. The clinical examination, test and questionnaires will last around 90 min.

The primary outcome will be the distance walked during the 6MWT, which is widely used in stroke studies [23, 24]. The 6MWT provides an objective measure of functional ability, endurance, and walking ability in people with physical impairments and stroke sequelae [25]. In addition, the 6MWT is a predictor of individual community walking activity, ambulation, and social integration in stroke survivors [26]. Patients will refrain from alcohol, tobacco, and caffeine consumption in the 24 hours before testing. The final score will be the distance walked during the 6MWT, and the rating of perceived exertion, assessed with the modified CR10 Borg scale from 0 to 10, will also be noted at the end of the test [27]. Secondary outcomes with the specific measurements are presented in Fig. 2.

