### Randomization and allocation

Eligible patients who agree to participate will be asked to give their written informed consent, and will then be randomized into the HB-PAI group or CG. We will randomize the patients at the first clinical examination. The randomization process will be ensured using a secure internet connection with access by individual user ID and password and encrypted data transmission to the randomization platform of the Clinical Research Unit of the Limoges University Hospital. Only the study methodologist will complete and keep the randomization list on a secure server. This randomization list will be balanced by blocks of variable size and will not include a stratification factor. All actions carried out on this platform and the identity of the person who made the changes will be automatically archived by audit trail procedure. As soon as a patient is randomized, an email will automatically be sent to all organizers of the study, i.e. the Clinical Research Assistant, Data Manager and Principal Investigator. No strategy was provided for preventing a potential imbalance between intervention and control group allocation.

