### Statistical analysis

We will describe quantitative variables as mean ± standard deviation, and qualitative variables as numbers, percentages and 95% confidence intervals. We will present the study flow diagram and the patient characteristics for each group. The scientific council and the Biostatistics clinical research department will elaborate a detailed statistical analysis plan.

The analysts will compare the 6MWT distance between each group using either the matched Student’s *t* test or non-parametric Mann–Whitney test, depending on whether the data follow a normal distribution. They will also compare the qualitative variables using Pearson’s chi-squared test or Fisher’s exact test. We will compare the distributions of quantitative variables using Student’s *t* test or non-parametric Man-Whitney test.

The analysts will calculate the univariate Spearman coefficient for correlation between two quantitative variables. They will also compare data between T0, T1 and T2 in both groups using the Friedman test and Wilcoxon matched pairs test. Multivariate linear regression analysis may be performed, taking prognostic factors into account.

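### The stated primary comparison of 6MWT distance carries no baseline term, although T0 distance is measured in every patient and randomization is unstratified

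*Protocol article*

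**What the plan says.** - **Endpoint (Outcomes).** The primary outcome is a distance: "The final score will be the distance walked during the 6MWT". Assessments are scheduled at T0, 6 months (T1) and 12 months (T2), so each patient should have a T0 distance.
- **Primary test (Statistical analysis).** "The analysts will compare the 6MWT distance between each group using either the matched" Student's t test or the Mann–Whitney test, depending on normality. No covariate is named, and neither test can carry one.
- **Adjustment (Statistical analysis).** "Multivariate linear regression analysis may be performed, taking prognostic factors into account". The factors are not listed and T0 distance is not mentioned.
- **Use of T0 (Statistical analysis).** "They will also compare data between T0, T1 and T2 in both groups using the Friedman test and Wilcoxon matched pairs test". These tests describe change over time and do not give a baseline-adjusted treatment effect.
- **Randomization (Randomization and allocation).** The list is blocked but "will not include a stratification factor".
- **Eligibility (Participants).** Entry requires "Functional Ambulation Classification score ≥2" with no upper limit and a stroke less than 6 months old. Disorders limiting gait, and cardiopulmonary disease preventing effort, are excluded.

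**The concern.** Walking distance at T0 is probably among the strongest predictors of walking distance later. When it is left out of the primary comparison, two things follow.

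1. The variation in follow-up distance that T0 explains stays in the error term, so the confidence interval is wider than the data require.
2. Any chance difference between arms at T0 passes, in proportion to r, into the estimated treatment effect. With 42 per arm and no stratification, a noticeable difference can arise.

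The optional regression does not remedy this, because nothing commits it to including T0 distance. The word 'matched' adds a further difficulty: a matched t test does not fit two independent randomized groups, so the stated primary method needs rewording in any case.

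**Working it through.** **Inputs from the article.** 36 per group before inflation, 42 after; 80% power; two-sided alpha 5%; 30% improvement; 'variance' of 30%. **Assumed input.** The correlation r between T0 and follow-up 6MWT distance. The article gives no value, so r is shown from 0.3 to 0.8.

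**Step 1: the plan's own figure.** With n = 2(1.96 + 0.842)²σ²/δ²:
- 30% read as the SD: 2 × 7.849 × 0.09/0.09 = 15.7, so 16 per group.
- 0.30 read as the variance: 2 × 7.849 × 0.30/0.09 = 52.3, so 53 per group.

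Neither gives 36, which is a separate matter. What 36 per group does imply is a standardised difference of √(2/36) × 2.802 = 0.66 (0.67 with the exact t test) at 80% power. That is used below because it is the effect size consistent with the stated n and power. The inflation step reproduces: 36 × 1.15 = 41.4, so 42.

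**Step 2: precision and power with T0 as covariate.** ANCOVA has residual variance (1 − r²)σ², so the CI width ratio is √(1 − r²) and the effective standardised effect is 0.67/√(1 − r²). One degree of freedom is lost, which is negligible here.

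| r (assumed) | 1 − r² | CI width ratio | CI narrower by | Power at 36 per arm, 0.67 SD | Detectable difference at 80% power |
|---|---|---|---|---|---|
| none (unadjusted) | 1 | 1 | – | 80% | 0.67 SD |
| 0.3 | 0.91 | 0.954 | 5% | 84% | 0.64 SD |
| 0.5 | 0.75 | 0.866 | 13% | 90% | 0.58 SD |
| 0.7 | 0.51 | 0.714 | 29% | 97.5% | 0.48 SD |
| 0.8 | 0.36 | 0.600 | 40% | 99.7% | 0.40 SD |

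**Step 3: chance imbalance at T0.** With 42 per arm, the SE of the T0 mean difference is √(2/42) = 0.218 SD. The probability of a difference above 0.3 SD in either direction is 2 × [1 − Φ(0.3/0.218)] = 17% (20% with 36 per arm). A T0 difference of 0.3 SD moves the unadjusted estimate by r × 0.3 SD: 0.09, 0.15, 0.21 and 0.24 SD at r = 0.3, 0.5, 0.7 and 0.8. As a share of 0.67 SD that is 13, 22, 31 and 36%.

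**Step 4: if change from T0 was meant.** A change score has variance 2(1 − r)σ². At r = 0.7 this is 0.60 against 0.51 for ANCOVA. The CI ratio is √(0.51/0.60) = 0.92, so ANCOVA would narrow the interval by about 8%.

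**The case against.** **The unadjusted test is not wrong.** A reader might infer that the primary analysis is biased or has an inflated error rate. The article does not support that: over all randomizations, a two-group test of independent arms is unbiased with 5% type I error. What is lost is precision, and accuracy given the imbalance that actually occurs.

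**The matter may belong to the SAP.** The article announces a detailed SAP, which is not shown. But it does not merely stay silent: it names the primary test and makes adjustment optional. An SAP would have to replace that test, not fill in detail.

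**T0 may already be used.** 'Matched', and the hypothesis of a 30% improvement, could point to change scores. This stands as an ambiguity. Against it, the text compares distance between groups, offers Mann–Whitney as the alternative and never names change as the endpoint. ANCOVA would still be more efficient, but by less (Step 4).

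**The trial may have ample power.** If 30% is the SD, the standardised effect is 1 and unadjusted power at 36 per arm is already 99%. If 0.30 is the variance, it is about 63%. The article does not settle which, so neither ample power nor a serious shortfall can be claimed. A smaller effect such as 0.5 SD would show unadjusted power of 55%, but the protocol posits no such effect.

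**Two further stronger readings.** A reader might take "No strategy was provided for preventing a potential imbalance between intervention and control group allocation" as conceding that nothing guards against prognostic imbalance. The sentence concerns allocation to groups and follows a description of blocking; only the absence of stratification is stated. A reader might also infer that the more favourable of the adjusted and unadjusted results could be reported as primary. The article names the two-group test for 6MWT distance, and nothing lets the regression replace it.

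**Conclusion.** The point holds as a recommendation to improve the stated primary analysis; the planned test is not invalid. The article fixes a comparison without a baseline term, although T0 distance is measured and randomization is unstratified. The interval would narrow by about 5% at r = 0.3 and 40% at r = 0.8. Power at 0.67 SD and 36 per arm would rise from 80% to between 84% and 99.7%.

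These figures rest on r, which is assumed, and on the effect size implied by 36 per group, because the stated 30% inputs do not reproduce that number. Wide variation in T0 walking ability is plausible from the entry criteria, but no T0 SD is given and the gait exclusions narrow the population somewhat. The direction of the gain does not depend on these assumptions: apart from one degree of freedom, ANCOVA is at least as precise as the unadjusted comparison for any r.

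**What to change.** - Name as the primary analysis an ANCOVA, or an equivalent mixed model, of follow-up 6MWT distance with group and T0 6MWT distance as pre-specified terms. T0 must be the measurement taken before the intervention starts.
- For this outcome, let it replace both the 'matched' t test and the optional regression. If any further prognostic factors are wanted, list them in advance.
- Keep the unadjusted independent-samples t test or Mann–Whitney test as a sensitivity analysis.
- Retain a provision for marked non-normality within the adjusted analysis, for example rank-based ANCOVA or a bootstrap confidence interval.

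The cost is a wording change to the stated primary analysis, dated and documented before database lock. T0 distance is already scheduled for every patient. Visits, assessments and sample size do not change, so it can still be done with 50 of 84 patients enrolled.

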### Data monitoring and auditing

The Ticaa’dom intervention protocol does not present a major risk for participants. Thus, we will not establish an independent data monitoring committee (IDMC). A clinical research technician will always conduct data monitoring and auditing, and will be confirmed 3 weeks before the appointment. The auditing will ensure research quality, results validity and compliance with French laws and regulations.

### Harms

Pursuant to the French law regulating the Ticaa´dom protocol, the research team will report adverse events in the three following cases:Adverse event: any harm occurring to a person who is amenable to biomedical research, regardless of whether the event is related to the research (Article R.1123-39 of the Public Health Code)Serious adverse event: any adverse event that could cause the death or endanger the life of the participant, cause a significant or lasting disability or handicap, or lead to hospitalization or a congenital anomaly or malformation (article R.1123-39 of the Public Health Code)Unexpected adverse event: any adverse event where the cause, evolution, and/or severity is inconsistent with the information contained in the French protection committee applications (article R.1123-39 of the Public Health Code)

### Interruption and exclusion conditions

Authors will be empowered to remove any participant in the case of stroke relapse, serious adverse event, participant desire to withdraw, or development of any other condition impeding the participant’s independent movement. Patients who die will not be included in the analysis; patients who withdraw consent will be excluded from the study.

If the participant is absent at the evaluation or clinical examination, they will be excluded from the study, and will be followed up to determine the cause of the absence. We will take missing data into consideration by the last observation carried forward (LOCF) strategy. The PA therapist will document all withdrawals on the CRF along with the supplementary clinical information. A 15-day maximum period of pause will be tolerated.

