### Control group

The CG will receive traditional follow up, including a medical appointment at 1 and 6 months after the hospital discharge. The CG will not monitor their PA and will not receive home visits or telephone calls. After inclusion, the PA therapist will give an explanation of PA recommendations and the benefits of an active lifestyle on stroke recurrence prevention.

The Ticaa’dom protocol is a strategy to monitor and incite PA at home in stroke survivors. In this context, ambulatory care in stroke rehabilitation – i.e. physiotherapy – will be authorized during the trial for both groups. In contrast, intensive after-discharge rehabilitation programs conducted by the hospital’s rehabilitation service or participation in other PA programs will not be allowed during the experiment. If hospital rehabilitation is mandatory, the participant will be excluded from the study.

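### Randomised patients can leave the study or the analysis because of later events tied to walking ability, and the absence rule is not reconciled with the LOCF rule beside it

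*Protocol article*

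**What the plan says.** Randomisation takes place at the first clinical examination (Randomization and allocation), so each rule below acts on patients already randomised.

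- **Death and withdrawal** (Interruption and exclusion conditions): "Patients who die will not be included in the analysis; patients who withdraw consent will be excluded from the study".
- **Missed assessment** (same section): "If the participant is absent at the evaluation or clinical examination, they will be excluded from the study".
- **Removal at discretion** (same section): "Authors will be empowered to remove any participant in the case of stroke relapse, serious adverse event, participant desire to withdraw". The sentence goes on to cover any other condition that impedes independent movement.
- **Hospital rehabilitation** (Control group; the paragraph concerns both groups): "If hospital rehabilitation is mandatory, the participant will be excluded from the study".
- **Missing data** (Interruption and exclusion conditions, immediately after the absence rule): "We will take missing data into consideration by the last observation carried forward (LOCF) strategy".
- **Visit window** (Outcomes): "If the participant cannot attend the medical appointment, it will be delayed for a maximum of 3 days".

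The primary outcome is 6MWT distance, assessed at T0, 6 months (T1) and 12 months (T2). The article does not say that a removed or excluded patient stays in the analysis.

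**The concern.** Randomisation makes the two groups comparable at entry. A comparison restricted to patients who later stay in the study keeps that property only if leaving is unrelated to outcome, or if it works in the same way in both arms. Neither can be taken for granted here.

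First, the reasons for leaving (death, relapse, serious adverse event, loss of independent movement, return to hospital rehabilitation) bear directly on how far a patient can walk. Removing someone for impeded movement comes close to selecting on the primary outcome.

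Second, contact is unequal. The programme arm has weekly calls and a home visit every 3 weeks for 6 months. The control arm has medical appointments at 1 and 6 months and no calls or visits. Both the detection of events that can trigger removal and attendance at assessments may therefore differ by arm. Part of the removal is also discretionary, and the only blinding described is that of outcome evaluation.

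Third, two adjacent sentences appear to give different instructions for the same patient. Someone absent at T1 or T2 is excluded by one sentence and is the obvious case for LOCF under the next. Two analysts could build different analysis sets from this text.

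**Working it through.** **1. The rules side by side**

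| Event after randomisation | Stated consequence | Out of the analysis? | Can LOCF apply? |
|---|---|---|---|
| Death | left out of the analysis | yes, explicitly, even if a T1 distance exists | no |
| Absence at an assessment | excluded from the study | not stated | only if exclusion means that follow-up stops |
| Withdrawal of consent | excluded from the study | not stated | as above |
| Hospital rehabilitation becomes mandatory | excluded from the study | not stated | as above |
| Relapse, serious adverse event, impeded movement | may be removed, at discretion | not stated | not stated |

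For a patient absent at T2, LOCF would carry the T1 distance forward; for one absent at T1, it would carry T0. If exclusion takes the patient out of the analysis, there is nothing to fill. If it only ends follow-up, the two sentences are compatible, but a patient absent at T1 is then not asked back at T2. The text does not choose between these.

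**2. What the 15% addition covers**

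The article adds 15% to 36 per group: 36 × 1.15 = 41.4, so 42. Losing 15% of 42 leaves 42 × 0.85 = 35.7, in effect the planned 36. The addition therefore protects precision against about that much loss. It does nothing about bias. The article gives no expected exclusion rate by arm.

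The 36 itself is not reproduced from the stated inputs. A 30% difference with an SD of 30% gives 16 per group (17 by the exact *t* test), and a variance of 0.30 gives 53 (54 exact). Thirty-six per group corresponds to a standardised difference of 0.67, used below only as a yardstick. The present point does not depend on it.

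**3. Illustration of bias (all rates assumed)**

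Take no true effect. In each arm a share q = 0.15 of patients has an event costing 1 SD of 6MWT, and a fraction p of those patients is removed. The mean of the retained patients, relative to patients without an event, is

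m(p) = −q(1 − p) / (1 − qp).

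| Removed, HB-PAI v CG | m in HB-PAI | m in CG | Spurious difference |
|---|---|---|---|
| 100% v 50% | 0 | −0.075/0.925 = −0.081 | +0.081 SD |
| 90% v 30% | −0.015/0.865 = −0.017 | −0.105/0.955 = −0.110 | +0.093 SD |
| equal p | same | same | 0 |
| 50% v 100% | −0.081 | 0 | −0.081 SD |

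Against the yardstick, 0.081/0.67 is about 12%.

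**4. Effect on the type I error (assumed rates)**

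Suppose excluded patients walk 1 SD less than retained ones, and fractions e₁ and e₀ are excluded in the two arms. With the full-arm mean set at 0, the retained mean is e × 1 SD, so the bias is (e₁ − e₀) SD. Simulation from 42 per arm (20,000 trials per row, two-sided 5% *t* test) gave:

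| e₁ v e₀ | Bias | Type I error |
|---|---|---|
| 15% v 15% | 0 | 5.0% |
| 25% v 10% | 0.15 SD | about 9% |
| 30% v 10% | 0.20 SD | about 12% |
| 25% v 5% | 0.20 SD | about 13% |

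What matters is the imbalance between arms, not the total excluded.

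**The case against.** The best defence is textual. The section uses two expressions: deaths are left out of the analysis, while withdrawals and absentees are excluded from the study. Read as a deliberate distinction, the second means that follow-up ends, and LOCF then fills the later values. On that reading only deaths are dropped. This has force: a flat contradiction with LOCF is not established. But the article never states the distinction, so the ambiguity remains, and the death rule is explicit.

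The article also promises a detailed analysis plan and never claims an intention-to-treat analysis. A reader might infer a broken intention-to-treat commitment; there is none to break. Deferral does not settle the matter, though. These exclusion rules are already fixed here, and outcome data never collected from an excluded patient cannot be restored by a later plan.

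Two further inferences are tempting and should not be drawn:

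- **That the bias favours the programme.** More frequent contact may reveal more events in HB-PAI, but it may also improve attendance there. Both arms are assessed at T0, T1 and T2, and the contact difference lasts only for the first 6 months. The documents do not fix the sign.
- **That anyone assessed more than 3 days late is lost.** The Outcomes section caps the delay. It does not say that a later visit counts as absence or that its data are discarded, and it has appointments confirmed 3 weeks ahead. No estimate of loss from lateness can be drawn from the text.

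Finally, removal for relapse or a serious adverse event is a power given to the authors and is not automatic.

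**Conclusion.** The point stands and should be settled before analysis, because these rules decide who enters the primary comparison. Three things are established. Deaths are explicitly left out of the analysis. The other exclusions and removals follow randomisation and relate to walking ability, and the article does not separate ending follow-up from leaving the analysis. The absence rule and the LOCF sentence conflict unless exclusion means only that follow-up stops.

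The comparison of retained patients can therefore be biased, but neither the size nor the direction can be found from the documents. The spurious 0.08 SD rests on assumed values: a 15% event rate, a cost of 1 SD, and 100% v 50% removal. Equal removal gives zero, and the reverse imbalance reverses the sign. The type I errors of about 9% to 13% likewise rest on assumed unequal exclusion rates and a 1 SD deficit.

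**What to change.** Amend the protocol, and carry the same wording into the analysis plan:

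- All randomised patients are analysed in their allocated group.
- Leaving the programme, relapse, a serious adverse event, rehospitalisation or a missed visit does not remove a patient from the analysis. T1 and T2 assessments are still sought unless consent for follow-up is withdrawn.
- All 6MWT data collected before death or withdrawal are kept.
- Delete the rule "Patients who die will not be included in the analysis" and the exclusion for absence. Reconcile the hospital-rehabilitation sentence under Control group with the same principle.
- State that the missing-data rule applies to every randomised patient with a missing 6MWT, and state separately how deaths are handled. If LOCF is retained, carrying a distance forward past death treats the patient as still walking it, so this has to be an explicit choice.
- Report deaths and missing assessments by arm.
- Keep any analysis of retained patients as a sensitivity analysis only.
- In the Outcomes section, say that an assessment done after the 3-day limit is still used, with its actual date recorded.

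This concerns follow-up and analysis only; it does not alter who stops the programme or what care a patient receives. The cost is a wording change and some effort to recall patients, and some late or off-programme assessments will enter the analysis. With 50 of 84 already enrolled, data from any patients already excluded may not be recoverable; their number should be reported by arm.

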On the subject of home-based PA in the subacute phase of stroke recovery, Studenski et al. [20] compared the motor control, balance, endurance and mobility of the upper and lower extremities following a 12-week cycle ergometer program. Compared to usual care, the intervention brought about better gains (*P* = 0.0056), in the form of improved scores in the Barthel Index (BI) and Balance Berg Scale (BBS), better peak aerobic capacity, improvements in the up-and-go test (TUG) and 6MWT, and better physical and social scores in the medical outcomes of the Short-Form 36-item (SF-36) questionnaire, better strength and improved upper extremity skills in subscales of the Stroke Impact Scale (SIS) and in quality of life (QOL) [20, 21].

To our knowledge, no study has yet investigated the effects of home-based PA incentive programs outside of standard and structured therapy during the subacute phase of stroke recovery. The investigated home-based PA incentive program (Ticaa´dom) could be a useful strategy to increase daily PA, to change sedentary lifestyle over time, and to establish PA monitoring after stroke. The primary aim of this planned study is to evaluate how a 6MWT is affected by the Ticaa´dom program over 12 months in the subacute phase of stroke recovery. We hypothesize that the PA incentive program will increase daily PA and independence among stroke patients. The secondary objective is to evaluate whether and how well patients keep practicing PA at 6 months after the end of the PA incentive program.

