### Study design and settings

Ticaa’dom is a comparative prospective, observer-blinded, monocentric, parallel, randomized controlled clinical trial. The Neurological and Physical Medicine and Rehabilitation Services of Limoges University will conduct this study in the Limousin region of France.

Ticaa’dom will also include a home-based 12-month post-discharge study conducted by professional PA therapists. The protocol will include two groups: the home-based physical activity incentive group (HB-PAI) and the control group (CG). The HB-PAI will include a physical activity incentive and education program for the first 6 months, followed by 6 months of traditional follow up. The CG will receive traditional follow up for 12 months (Fig. 1).

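### Last observation carried forward is the only missing-data method named, in a population still recovering from stroke; it can bias the 6MWT comparison in either direction and conflicts with the exclusion rules beside it

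*Protocol article*

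**What the plan says.** The missing-data rule is in the Protocol article, Interruption and exclusion conditions: "We will take missing data into consideration by the last observation carried forward (LOCF) strategy". It is given without a reason and without a sensitivity analysis. The same section says "If the participant is absent at the evaluation or clinical examination, they will be excluded from the study" and "Patients who die will not be included in the analysis; patients who withdraw consent will be excluded from the study".

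The design around it:
- **Population (Participants):** "recovery from first ischemic or hemorrhagic stroke in all brain areas; stroke within <6 months".
- **Visits (Outcomes):** T0 after hospital discharge, T1 at 6 months, T2 at 12 months. The primary outcome is 6MWT distance.
- **Programme (Study design and settings):** "The HB-PAI will include a physical activity incentive and education program for the first 6 months, followed by 6 months of traditional follow up".
- **Aims (Background):** the primary aim is the effect on the 6MWT over 12 months. On persistence, "The secondary objective is to evaluate whether and how well patients keep practicing PA at 6 months after the end of the PA incentive program".
- **Sample size (Sample size calculation):** 30% improvement, a variance of 30%, two-sided 5%, 80% power, 36 per group, plus 15%, giving 42 per group.

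**The concern.** LOCF assumes that a patient's walking distance stops changing at the last visit attended. Here patients are in subacute recovery and the design itself expects the 6MWT to move. With two follow-up visits 6 months apart, every carried value is at least 6 months old. It is then analysed as a measurement, so the uncertainty of the filling is ignored.

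The two follow-up visits are affected differently. At T1 a missing patient is given no recovery since discharge. At T2 a patient lost after T1 is given the distance reached at the end of the programme, which assumes the maintenance of effect that the 12-month follow-up is there to assess. Both the 6-month and the 12-month 6MWT comparisons are exposed.

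The adjoining exclusion rules add a second problem. If absent patients leave the study, LOCF has little left to fill, and the analysis becomes one of completers, with selection bias of its own.

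**Working it through.** **1. The plan's own figure.** Per-group n = 2(1.960 + 0.842)²/d² = 15.70/d², where d is the difference divided by the SD.
- 30% difference, SD 30% (d = 1): 15.7, so 16.
- 30% difference, variance 0.30 (SD 54.8%, d = 0.548): 52.3, so 53.
- d = 0.667 (for example 30/45): 35.3, so 36.

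The stated 36 is not reproduced by either plain reading of the inputs. It corresponds to d of about 0.67, which is used below as a back-solved assumption. 36 × 1.15 = 41.4, so 42 as stated. Why 36 is not reproduced is a separate matter.

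**2. Assumptions.** The article gives no dropout rate by arm or period, and does not call its 15% dropout. All dropout, recovery and T2-effect values below are assumed. Dropouts are taken to have the same true course as completers, and the SD is taken as unchanged by carrying values forward. Where D = 30 is used, the unit is percent of control distance.

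**3. T1.** Let g be recovery in the control arm, D the true effect, and pT and pC the fractions lost before T1 in the programme and control arms.

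LOCF difference = (1 − pT)(g + D) − (1 − pC)g, so bias = (pC − pT)g − pT·D.

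- Equal dropout p: the difference is (1 − p)D whatever g is. At 15%, 30 becomes 25.5.
- g = 30, D = 30:

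| Lost, programme / control | LOCF difference (true 30) |
|---|---|
| 20% / 10% | 21.0 |
| 10% / 20% | 30.0 |
| 5% / 25% | 34.5 |

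- No true effect, recovery of 1 SD, 5% / 25% lost: (0.25 − 0.05) × 1 = 0.20 SD of false benefit.

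**4. Power at T1.** Two-sample t test, two-sided 5%, 42 randomised per arm, d = 0.67, equal dropout p before T1. LOCF uses 42 per arm and d(1 − p); observed-only uses 42(1 − p) per arm and d. With nothing missing, power is 85.9%.

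| p | LOCF | Observed patients only |
|---|---|---|
| 5% | 82.2% | 84.0% |
| 10% | 78.0% | 82.0% |
| 15% | 73.2% | 79.7% |
| 20% | 68.0% | 77.2% |
| 30% | 56.5% | 71.4% |

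The observed-only column holds if dropout is unrelated to outcome. At 15% the loss due to LOCF itself is 79.7 − 73.2 = 6.5 points.

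**5. T2.** With equal dropout in both arms, let p be lost before T1, q lost between T1 and T2, and D2 the true T2 effect. Control recovery cancels.

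LOCF difference = (1 − p − q)D2 + qD, so bias = qD − (p + q)D2. This is positive only when q/(p + q) > D2/D.

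| True D2 (D = 30) | p = 0, q = 15% | p = q = 7.5% | p = 15%, q = 0 |
|---|---|---|---|
| 0 | 4.5 | 2.25 | 0.0 |
| 15 | 17.25 | 15.0 | 12.75 |
| 30 | 30.0 | 27.75 | 25.5 |

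The same fading effect is overstated, unbiased or understated, depending only on when patients leave.

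**6. The rules side by side.** Under LOCF, a patient absent at T1 stays in with the T0 value. Under the exclusion rule, that patient leaves the study. Withdrawals are likewise excluded, and deaths are left out of the analysis. The section does not say which rule governs, or whom LOCF is meant to cover once these patients are removed.

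**The case against.** The strongest case against is that the exclusion rules come first. Read literally, they remove most patients with a missing visit, so few values would ever be carried and the figures above would scarcely apply. That stands as a limit on the size. It does not rescue the plan: what remains is a completer analysis, and the LOCF sentence then has almost no purpose.

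It may also be said that the Statistical analysis section defers detail to an analysis plan not shown here. It does, but this section has already fixed the method, so this is a stated choice and not an omission.

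Some stronger readings are tempting, and the document does not support them:
- *LOCF always dilutes the effect at T1.* This needs a true benefit and similar dropout. If the control arm loses enough more patients, the effect is inflated. The programme arm has weekly calls and regular visits that controls lack, so unequal loss is plausible, but no rates are given.
- *LOCF flatters the programme at T2 whenever benefit fades.* Patients lost before T1 carry T0 into T2 and pull the other way.
- *LOCF costs about 13 points of power.* That compares 73% with the 86% of a trial with nothing missing. Against observed patients at the same 15% loss, the cost is about 7 points.
- *LOCF presupposes the secondary objective.* As worded, that objective concerns continued physical activity, whereas these calculations concern 6MWT distance. The link is to the 12-month 6MWT follow-up.

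**Conclusion.** The concern holds in a limited form. LOCF is the only missing-data method named, and its frozen-value assumption is implausible for patients within 6 months of a stroke who are measured every 6 months. The direction of bias cannot be predicted from the document, so LOCF cannot be defended as conservative. Under equal dropout p, a true T1 effect shrinks by the factor 1 − p. At T2, again under equal dropout by arm, overstatement requires the share of losses occurring after T1 to exceed the ratio of the T2 to the T1 effect.

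The illustrative size is about 73% power against about 80%. It rests on a back-solved 0.67 SD, an assumed 15% loss before T1 in each arm, an unchanged SD, and dropout unrelated to outcome. The contradiction between LOCF and the exclusion rules needs no such assumptions. This should be fixed; the document does not establish that the trial's conclusions will turn on it.

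**What to change.** In Interruption and exclusion conditions, and in the analysis plan:

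1. Delete the LOCF sentence.
2. Reconcile the exclusion wording so that missing a visit or stopping the programme neither removes a randomised patient's collected data from the analysis nor ends later assessments. State separately how data collected before death or withdrawal of consent are used.
3. Analyse 6MWT at T0, T1 and T2 with a likelihood-based repeated-measures model with group, visit and group-by-visit terms, under missing-at-random. Keep T0 in the outcome vector, or use multiple imputation: with T0 only as a covariate, patients with neither T1 nor T2 drop out of the model.
4. Add delta-adjusted or reference-based sensitivity analyses.

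Step 3 depends on step 2: if a patient absent at T1 is still excluded, there is no T2 value for the model to use. The cost is a protocol edit, a little more analysis work, and follow-up of patients who miss a visit at visits already scheduled. No new type of measurement is needed. The article reports 50 of 84 patients enrolled, so at that stage the change could still be prespecified.
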